### Study aims

To establish whether diabetic patients with LVH have increased rates of brain atrophy and cognitive decline.To establish whether the specific LV geometric measures are associated with these brain volume changes.

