***Hypothesis 3: comparing brain volume and cognitive performance in participants with increased left ventricular mass and specific left ventricular geometric patterns.*** Analysis will be similar to that for LVH, except that patients will be divided on the presence or absence of specific morphometric measures. That is, analyses will be performed at each time-point (cross-sectional), and also longitudinally, to investigate change across time. Repeated-measures t-tests will determine the extent of brain volume loss across the two time-points and compared between groups. Correlation with cognitive performance will be performed as above. Unadjusted differences for clinical variables between groups will be assessed by *t*-test. Difference in laboratory data and left ventricular systolic function will be adjusted for age and sex by use of ANCOVA. Differences in left ventricular structure and geometry will be adjusted for age, sex, BMI, and systolic blood pressure as their major established covariates with further adjustment for duration of hypertension. Fisher’s Exact Test and odds ratios will be used to test differences for categorical variables. Logistic regression analysis will be used to derive odds ratios adjusted for covariates. Multiple regression analyses will be performed to assess relation of cognitive and brain volume measures to higher left ventricular mass independent of established covariates and duration of hypertension.

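### Hypothesis 3 names no covariate-adjusted model for brain volume loss by LV geometric pattern (Aim 2); the adjusted regression it does name covers LV mass only

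*Protocol article*

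**What the plan says.** All of this is in the protocol article.

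- **Aim.** The second item under Study aims is "To establish whether the specific LV geometric measures are associated with these brain volume changes".
- **Groups.** Statistical analysis, Hypothesis 3, is headed "comparing brain volume and cognitive performance in participants with increased left ventricular mass and specific left ventricular geometric patterns" and states that "patients will be divided on the presence or absence of specific morphometric measures".
- **Comparison of brain volume loss.** "Repeated-measures t-tests will determine the extent of brain volume loss across the two time-points and compared between groups". No covariates are attached.
- **Adjusted comparison of the heart measures.** "Differences in left ventricular structure and geometry will be adjusted for age, sex, BMI, and systolic blood pressure as their major established covariates", with duration of hypertension added as a further adjuster.
- **Adjusted models for brain and cognition.** Multiple regression is planned to "assess relation of cognitive and brain volume measures to higher left ventricular mass independent of established covariates and duration of hypertension". A separate sentence says "Logistic regression analysis will be used to derive odds ratios adjusted for covariates", without naming outcome or exposure.
- **Definition of geometry.** The Transthoracic echocardiography section defines LVH by a cut-off on LV mass indexed to height. It then uses relative wall thickness to assign a remodelling class. Geometric pattern is therefore a different variable from LV mass.

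**The concern.** This is an observational comparison, so the geometry groups will differ in more than geometry. The authors name age, sex, BMI and systolic pressure as the main covariates of LV structure and add duration of hypertension. Age and hypertension are also on their list of important adjusters in the Hypothesis 2 model for brain volume loss and cognitive impairment. A variable on both lists is a candidate confounder of geometry against brain volume.

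The covariate set is attached to two analyses: differences in LV structure and geometry, and brain volume and cognition in relation to LV mass. It is not attached to brain volume loss in relation to geometric pattern, which is what Aim 2 asks. If the t-test comparison is reported as planned, an older or more hypertensive geometry group could show greater atrophy for reasons unrelated to geometry.

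There is a second, smaller difficulty. The only groups that the Hypothesis 3 paragraph defines are the morphometric ones. Read naturally, it then compares LV structure and geometry between those groups, so the variable that forms the groups is also an outcome.

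**Working it through.** The protocol gives no power or effect size for Hypothesis 3, so there is no figure to reproduce. The check has three parts.

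**1. Which analyses could supply an adjusted geometry-versus-brain result?**

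| Analysis in the article | Exposure | Outcome | Clinical covariates |
|---|---|---|---|
| Hyp. 3, repeated-measures t-tests | geometry group | brain volume loss | none named |
| Hyp. 3, analysis similar to that for LVH (refers to Hyp. 1) | geometry group | brain volumes | none; intracranial volume for regional volumes |
| Hyp. 3, differences in LV structure and geometry | group | LV structure and geometry | age, sex, BMI, systolic pressure, duration of hypertension |
| Hyp. 3, multiple regression | higher LV mass | brain volume, cognition | established covariates, duration of hypertension |
| Hyp. 3, logistic regression | not named | not named | covariates, not listed |
| Hyp. 2, multivariate regression | brain volume loss, related to cognitive impairment | cognitive impairment | age, education and others; cardiac indices as adjusters |
| Hyp. 2, dose-related multivariate analysis | extent of cardiac impairment | not specified | not listed |

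No row combines geometric pattern as exposure, brain volume change as outcome and the stated covariates.

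**2. How much could the missing adjustment matter?**

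Inputs from the Sample size section: 140 evaluable patients, 30% with specific geometric changes, two-sided alpha 0.05. Assumed, because the article gives no value: one linear combination of five covariates explains a share R² of both the LV measure and brain volume change, in the same direction, and geometry has no effect of its own.

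Splitting a standard normal LV measure at its upper 30% (z = 0.524, density φ(z) = 0.3477) separates the groups by

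φ(z)/0.3 + φ(z)/0.7 = 1.159 + 0.497 = 1.656 SD.

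The spurious difference in brain volume change is then R² × 1.656 SD. With groups of 42 and 98 its standard error is about √(1/42 + 1/98) = 0.184 SD. The rejection probability is Φ(m − 1.96) + Φ(−m − 1.96), where m is the difference divided by its standard error.

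| Assumed R² | Spurious difference (SD) | m | Unadjusted, formula | Unadjusted, simulated | Adjusted, simulated |
|---|---|---|---|---|---|
| 5% | 0.083 | 0.45 | 7% | not run | not run |
| 10% | 0.166 | 0.90 | 15% | 14% | 5% |
| 20% | 0.331 | 1.80 | 43% | 42% | 5% |
| 30% | 0.497 | 2.69 | 77% | 78% | 5% |

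The simulations used 2,000 trials per row. Formula and simulation agree.

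**3. Is the comparison of LV structure informative?**

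Simulated with 140 or 168 patients, splits at 30% or 50%, and covariates explaining 0 to 60% of the grouping measure (500 trials per setting), the covariate-adjusted test rejected as follows:

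- outcome is the measure that defines the groups: 100% in every setting;
- another LV measure, correlation 0 with the defining one: 3% to 6%;
- correlation 0.2: 12% to 52%;
- correlation 0.4: 45% to 100%.

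The result is fixed in advance only for the defining measure.

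**The case against.** Two stronger readings are tempting, and the document does not support either.

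*The adjustment never reaches the brain analyses.* A reader might infer this from where the covariate sentence stands. It is not so. The last sentence of Hypothesis 3 applies the established covariates and duration of hypertension to brain volume and cognition against LV mass. LV mass is also part of the exposure in the third study hypothesis. Adjusted logistic regression is planned too, and Hypothesis 2 adds a multivariate analysis of cardiac impairment. What remains is the narrower gap: none of these names geometric pattern as exposure with brain volume change as outcome. LV mass cannot stand in for pattern, because concentric remodelling is classified separately from concentric LVH and depends on relative wall thickness.

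*The comparison of LV structure must come out positive.* This holds only for measures that define the split. Other LV measures need not differ, and 24-month change in LV structure is not fixed by the grouping. The sentence also does not name its groups. If patients were compared by cognitive status, nothing would be circular. The morphometric groups are the natural reading, not the only one.

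It can also be said that comparing cardiac characteristics between groups is ordinary descriptive reporting, and that a condensed article leaves detail to an analysis plan. The first is fair, and labelling the comparison as descriptive would settle it. The second carries less weight here, because the article does name a method for brain volume loss by geometry group, and that method carries no clinical covariates.

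**Conclusion.** The point stands in its narrow form. For Aim 2, the only method named for brain volume loss by geometric pattern is a set of t-tests compared between groups. The covariates that the authors call established are explicitly applied to LV mass but not to pattern.

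The size of any bias cannot be derived from the protocol. Under the assumed sharing of covariates, the false-positive rate runs from about 7% at R² = 5% to about 78% at R² = 30%, against 5% nominal. These figures assume that the same covariate combination drives both variables in the same direction and that the groups come from a split of one continuous measure. Weaker alignment gives less inflation, and no sharing gives none. They show why adjustment is needed and do not forecast this study's error rate.

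The circular comparison is a secondary matter of labelling: uninformative for the defining measures, possibly informative for others. Overall weight is modest, because Hypothesis 3 is secondary and an adjusted LV mass analysis is already planned.

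**What to change.** 1. In Hypothesis 3, replace the compared t-tests with a linear model of brain volume change on geometric pattern, adjusted for age, sex, BMI, systolic blood pressure and duration of hypertension. Keep the intracranial volume adjustment for regional volumes. Fit the corresponding model for cognitive score. Report both beside the LV mass regression already planned; the unadjusted differences can be shown as well. The model also gives a direct contrast between groups.
2. Name the groups for the comparison of LV structure and geometry. If they are the morphometric groups, present the measures that define them as description, without p-values.

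The cost is the rewording of about two sentences. No new variables are needed beyond those on which the plan already relies: height and weight, ambulatory blood pressure, age, sex and hypertension history are collected at baseline, and duration of hypertension is already a planned adjuster. With four geometry classes (three terms), five covariates and an intercept, 140 patients leave 140 − 9 = 131 residual degrees of freedom, so the model is affordable.

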## Discussion

The D2 study will aim to improve the understanding of two of the major causes of death, disability and reduced quality of life in our society: diabetes and dementia. In an ageing population, it is vitally important that we increase our knowledge of the relationships between cardiovascular disease and cognition. We have the means to identify a potentially treatable risk factor in the causation of cognitive impairment. The study will provide unique information on the relationship between LVH and dementia in type 2 diabetes, and whether cardiac structural and functional abnormalities contribute to increased brain atrophy and cognitive impairment. Brain volume changes may precede cognitive changes, providing a potential for early diagnosis and intervention. A large proportion of these patients may have associated or superadded Alzheimer’s pathology. These patients provide a high risk cohort requiring urgent intervention to prevent increasing dependence and disability. The identification of people at risk of cognitive impairment and dementia will allow for both secondary prevention and early intervention. With the advent of aggressive risk management strategies for cardiovascular disease, identification of these patients will allow them to be treated early in their disease course, ideally before they develop cognitive decline.

## Abbreviations

3D: Three-dimension
APOE: Apolipoprotein E
ASE: American Society of Echocardiography
BMI: Body mass index
CIMT: Carotid intima media thickness
DWI: Diffusion weighted imaging
ECG: Electrocardiogram
eGFR: Estimated glomerular filtration rate
FLAIR: Fluid-attenuated inversion recovery
GAD-7: Generalized anxiety disorder questionnaire
LVH: Left ventricular hypertrophy
MET: Metabolic equivalents minute
MPRAGE: Magnetization-prepared rapid gradient-echo
MRI: Magnetic resonance imaging
PHQ-9: Patient health questionnaire
SWI: Susceptibility-weighted image
TTE: Transthoracic echocardiography
